### Baseline evaluation

After informed consent is obtained, participants will complete a baseline questionnaire online at the secure study website. Baseline blood draws will be performed on-site at the conclusion of a participant’s scheduled work shift. All plasma samples will be shipped to the University of Michigan for processing and analyses for the detection of 20 commonly-used chemotherapy drugs.

### Spill reporting

If a spill occurs in the ambulatory oncology infusion center throughout the 4-year study period, participants will return to the secure study website and complete a brief spill report. They will also have blood drawn at the end of the shift to obtain drug levels. A second blood draw will be performed 24 hours after the first one (or the next available business day) to obtain estimated peak and trough values, respectively.

### Plasma analyses

Participants will provide blood for plasma sampling at the baseline and post-intervention assessment, as well as with the occurrence of any reported drug spill during the study. The procedures below are used for all obtained samples. At the end of a nurse’s shift, the nurse will report to the participating site’s designated phlebotomy area. Trained and credentialed phlebotomy staff will perform venipuncture using standard technique and place whole blood into 5-mL heparinized tubes. Cells will be removed from plasma by centrifugation for 10 minutes at 1,000 to 2,000 × g using a refrigerated centrifuge. Plasma will then be pipetted into a clean polypropylene tube and stored in a −20°C or lower freezer. After plasma samples are frozen, they will be shipped by next-day air and on dry ice to the University of Michigan.

To measure levels of potentially hazardous drugs from the obtained samples, a specific and highly sensitive liquid chromatography-electrospray ionization-mass spectrometry (LC-ESI-MS) method will be established. We will focus our efforts on the 20 drugs that are the most commonly administered agents in ambulatory oncology settings with chemical properties suitable for analysis. However, as methods emerge for the measurement of other drugs, we will consider these as nurses report exposure outside of our original list of drugs. Signals from the test drug will be monitored under the multiple reaction monitoring mode of the LC-ESI-MS for quantification [33]. Ionization mode, precursor to product ion transition, ion source parameters (potential, gas, temperature, and so on), mobile phase, and column will be optimized and selected under direct infusion and flow injection analysis of the pure compound. The selection of extraction method, including protein precipitation, liquid-liquid extraction, and solid phase extraction, will depend on the drug properties (for example, acidity content, lipophilicity, aqueous solubility and chemical stability). The most efficient and specific extraction method will be used for sample preparation.

Drugs with similar properties and similar measurement methods (using the same column, same mobile phase, and similar extraction conditions) will be grouped into one method to simultaneously detect several drugs in one injection. This technique will greatly enhance the screening throughput. Each sample batch processed will include plasma samples from healthy, unexposed volunteers to ensure calibration. The established method for detecting multiple test drugs in one injection will be evaluated for linearity, specificity, and sensitivity according to guidance from the Food and Drug Administration [34]. Results from the LC-ESI-MS analyses will be entered into RedCAP, a secure, Health Insurance Portability and Accountability Act (HIPAA)-compliant cloud-based data management platform [35]. Specimens and survey data will be linked by unique study identifiers.

### Statistical analysis

Survey data will be stored on the password-protected, user-authenticated encrypted server behind a firewall. Our hypotheses are focused on the efficacy of an audit and feedback intervention to nurse participants. A total of 382 nurses are expected to be sampled from 11 sites. Each site is randomized into either control or intervention condition. Because the nurses within the same site are likely to show correlated outcomes, we will use linear mixed-effects models to account for the intraclass correlation for the proposed cluster randomized trial [36,37]. More specifically, we will use a random intercept model in which a variable *site* is created to identify the sites, and then adding *site* as a random effect to the mixed model.

Aim 1 evaluates the efficacy of audit and feedback to improve recommended PPE use (compared with an educational video). The outcome variable of the fixed-effect structure is the PPE use scores. The predictor of the fixed effect is the intervention indicator variable. The data from the PPE use questionnaire and demographics variables that are included in the fixed-effect structure to increase the precision of estimates. The random effect in the model is the *site* variable. We assume the *site* variable follows a normal distribution with mean zero and is independent of the error term in the mixed model. The hypothesis is that there will be a significant intervention effect such that nurses in sites receiving the treatment, in addition to the web-based educational module, will report higher PPE use scores compared to nurses in sites randomized to receive only the control. Means within time will be computed as descriptive statistics to help describe the effect.

Aim 2 will determine whether knowledge about PPE use and perceived risk of drug exposure mediate the effect of the treatment intervention on PPE use. The hypothesis is that the effect of the treatment on PPE use will be at least partially mediated by knowledge and perceived risk. To measure the mediation effect, we fit two linear mixed models. The first model is the same model we use in Aim 1. The second model adds the two potential mediators in the first model. The mediator effect is measured as the difference in the coefficients of the intervention variable between the two models. A 95% confidence interval is calculated for the estimate. If the confidence interval does not cross zero, it shows that mediation effect is statistically significant.

Aim 3 will determine whether the treatment intervention effect on PPE use is moderated (strengthened or weakened) by personal (experience, education, certification) and organizational factors (workloads, practice environments, safety organizing). We will use mixed model analyses that include receipt of the treatment intervention, the moderator variables, and the products of treatment intervention receipt with the moderator variables as predictors of PPE use. Significance tests of the product terms between moderator and intervention variables will indicate whether moderation is present [38]. We hypothesize that at least one of these moderator variables will interact significantly with the treatment intervention. When the product term is significant, we will conduct a *post hoc* analysis by plotting the PPE use versus intervention at various levels of the moderator variables. Using graphical presentations, we can show the size of the intervention effect and how the effects vary based on the values of moderate variables.

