**ASSESSMENTS**										
Baseline Survey Demographics, PPE use, Plasma levels, PPE Knowledge, PPE Barriers, Moderators		X								
Primary Endpoint PPE use, Plasma levels							X			
Spill Assessments PPE use, Plasma levels			X	X	X	X	X	X	X	X

PPE: Personal protective equipment.

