### Conceptual framework

The study’s conceptual framework integrates theoretical, empirical, and pilot work that spans occupational health, health promotion, and organizational studies (Figure 1) [16-19]. The primary *outcome* of interest is PPE use using a valid and reliable measure described below [10]. The *interventions* are a 1-hour web-based educational module on hazardous drug safe handling with quarterly reminders about the educational content (control) or the web-based educational module with tailored messages plus quarterly feedback on hazardous drug spills and drug levels measured in the study population (treatment). Aim 1 will compare the control and treatment groups on PPE use. Next, we hypothesize the interventions will result in a) increased *knowledge* [20] about PPE use and b) increased *perceived risk* [21] of hazardous drug exposure. We hypothesize the treatment intervention will result in higher knowledge and perceived risk than the control intervention. In Aim 2, knowledge and perceived risk are considered mediators of the intervention effect because they are likely influenced by the intervention received and in turn will likely influence PPE use. Finally, preliminary work suggests a relationship between the *personal factor* of years of experience and PPE use. We will also explore additional personal factors, including nursing education and certification. Two *organizational factors* (nursing workloads and practice environments) are correlated to PPE use and hazardous drug exposure [11]. We will also explore a third factor of safety organizing behaviors [22]. In Aim 3, personal and organizational factors are considered moderators in our framework because they may strengthen or weaken the observed effect of the interventions on PPE use.

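### The Aim 2 mediation models reuse covariates chosen for Aim 1 precision and leave out baseline organizational factors that could confound the mediator-to-PPE association

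*Protocol article*

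**What the plan says.** The relevant text is in the protocol article, mostly under Statistical analysis.

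- **Aim 1 model.** PPE use is regressed on the intervention indicator with a random site intercept. On covariates the text says: "The data from the PPE use questionnaire and demographics variables that are included in the fixed-effect structure to increase the precision of estimates". The sentence is incomplete. I read it as the baseline PPE score plus demographics. The demographics are not listed.
- **Aim 2 models.** "The first model is the same model we use in Aim 1", and "The second model adds the two potential mediators in the first model". Then: "The mediator effect is measured as the difference in the coefficients of the intervention variable between the two models". Mediation is declared when the 95% confidence interval excludes zero.
- **Aim 3 models.** The personal and organizational factors appear here: "We will use mixed model analyses that include receipt of the treatment intervention, the moderator variables", with their products with the intervention.
- **Links to PPE use.** Under Conceptual framework, the two organizational factors ("nursing workloads and practice environments) are correlated to PPE use and hazardous drug exposure") are named as correlates. Preliminary work is said to suggest a relationship involving the personal factor "of years of experience and PPE use". Safety organizing is only to be explored.
- **Availability.** Table 1 lists the baseline survey as "Baseline Survey Demographics, PPE use, Plasma levels, PPE Knowledge, PPE Barriers, Moderators". Table 3 and the Potential moderators section confirm that each nurse reports these factors at baseline. Workload, practice environment and safety organizing are then averaged to site level.

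**The concern.** The difference in coefficients is the intervention's effect on the mediator multiplied by the mediator's adjusted association with PPE use. Randomization supports the first factor but not the second, because nobody assigns nurses their knowledge or perceived risk. Covariates picked to sharpen the Aim 1 estimate need not be the ones that make the second factor interpretable.

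A nurse in a better practice environment, for example, may know more about safe handling and also use PPE more often, without the first causing the second. If the intervention also raises knowledge, as the trial hypothesizes, the product is non-zero and the stated rule can call it mediation. The claim at stake is how the intervention works, not whether it works.

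**Working it through.** **1. The plan's own figure.** The only power statement is 80% for Aim 1 with 11 sites, a mean of 26 nurses, ICC 0.03 and a medium effect (d = 0.5 assumed, as no number is printed).

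- SE = 2√[(ICC + (1 − ICC)/m)/J] = 2√[(0.03 + 0.97/26)/11] = 0.156.
- Noncentrality = 0.5/0.156 = 3.20. On 9 df, two-sided 0.05, power is 0.811.

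The figure reproduces. It concerns Aim 1 only, but it supplies the design inputs used below.

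**2. What each model contains.**

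| Variable | Aim 2, model 1 | Aim 2, model 2 | Aim 3 |
|---|---|---|---|
| PPE questionnaire data, demographics | yes | yes | not stated |
| Knowledge, perceived risk (after intervention) | no | yes | no |
| Workload, practice environment, safety organizing | no | no | yes |
| Experience, education, certification | unclear | unclear | yes |

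**3. Expected spurious mediation.** The document gives no correlations, so these are assumptions. Let a be the mediator shift in SD. Let a common cause correlate r with the mediator and with PPE use at both times, and let baseline and endpoint PPE use correlate ρ = 0.5. The mediator has no true effect on PPE use. Adjusting for arm and baseline PPE use,

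spurious effect = a × r²(1 − ρ)/(1 − r⁴).

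With a = 0.5:

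- r = 0.2: 0.5 × 0.04 × 0.5/0.9984 = 0.010 SD
- r = 0.3: 0.5 × 0.09 × 0.5/0.9919 = 0.023 SD
- r = 0.4: 0.5 × 0.16 × 0.5/0.9744 = 0.041 SD

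Against an assumed total effect of 0.5 SD, these are about 2%, 5% and 8%.

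**4. How often the rule would declare mediation.** Simulation used 11 sites of 26 nurses, ICC 0.03, a random-intercept fit, no true mediator effect, and a Monte Carlo 95% interval for the indirect effect. Ranges are over repeated runs with slightly different data models.

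| Scenario (baseline PPE adjusted) | r = 0.2 | r = 0.3 | r = 0.4 |
|---|---|---|---|
| Shift 0.5 SD, common cause omitted | about 5% (4–6%) | about 10% (8–14%) | about 30% (26–32%) |
| Shift 0.5 SD, common cause included | 4–5% | 4–5% | 4–5% |
| Shift 0.2 SD, common cause omitted | 1–2% | 3% | 6–8% |

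If the intervention does not move the mediator, the mean difference is about zero whether or not the common cause is in the model.

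**5. A purely site-level cause.** At ICC 0.03 a site-level factor can correlate with PPE use at most √0.03 = 0.17. Letting one such factor carry all the between-site variance in both mediator and PPE use, with a 0.5 SD shift, gave false mediation of about 4% and a mean spurious effect below 0.01 SD.

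**The case against.** The strongest reply has four parts.

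- **Demographics are undefined.** The only personal characteristics in Table 3 are experience, education and certification, so these may already be in the model. A reader might infer from the separate Table 1 entries for demographics and moderators that they are left out. A schedule label is not a covariate list, so that inference is not supported. This part of the objection stands. Workload, practice environment and safety organizing are not demographics on any ordinary reading, so their omission remains.
- **No shared cause is documented.** The text links workload, practice environment and experience to PPE use, and says nothing linking any of them to knowledge or perceived risk. For safety organizing not even a PPE link is claimed. This stands: confounding is plausible, not demonstrated.
- **The organizational factors are defined as site means.** In that form they do negligible harm at the planning ICC, as step 5 shows. This stands for site means. The responses come from individual nurses, however, and nurse-to-nurse differences in perceived environment or workload are where a common cause could act.
- **A 0.5 SD shift may be generous.** Both arms see the same core module on the material that the knowledge test covers. This also stands. At 0.2 SD the problem nearly disappears.

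It cannot be said that the matter is simply left to an analysis plan. The article states the content of both Aim 2 models and the decision rule.

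**Conclusion.** The Aim 2 models are fixed with covariates chosen for another purpose, and at least three baseline factors that the trial already collects, two of them named as correlates of PPE use, are left out. The mediation conclusion is therefore open to avoidable confounding.

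The size depends wholly on assumed inputs. With baseline PPE use adjusted for and a 0.5 SD mediator shift, the false-mediation rate runs from nominal at r = 0.2 to about 30% at r = 0.4, with spurious effects of about 0.01 to 0.04 SD. It is at or near nominal for a 0.2 SD shift or a purely site-level cause.

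A reader might conclude that Aim 2 will report false mediation, or that the error rate is far higher still. Rates of 66–70% arise only at r = 0.4 with baseline PPE use left out of the model, whereas the plan includes PPE questionnaire data. The document supports a risk under plausible conditions, not a demonstrated bias. This is a minor improvement to a secondary aim.

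**What to change.** In both Aim 2 models, include:

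- the baseline PPE score, named as such;
- baseline knowledge and baseline perceived risk;
- each nurse's own baseline workload, practice-environment score and safety-organizing score;
- oncology experience, education and certification, if they are not already among the demographics (list the demographics to settle this).

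Use nurse-level values for these covariates, not site means. Three site means with the intercept and intervention would leave 11 − 5 = 6 between-site degrees of freedom. State that the mediation conclusion assumes no unmeasured mediator-outcome confounding, since measured covariates cannot rule it out. Leave the Aim 1 model as it is; the site-mean definition can stay for Aim 3.

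The cost is a sentence or two and a modest number of nurse-level degrees of freedom out of about 287 nurses, even after the 25% shortfall that the plan allows for (382 × 0.75 = 286.5). No new data are needed.

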#### Potential mediators

Both knowledge of PPE and perceived risk of hazardous drug exposure are hypothesized to mediate the potential effects of the intervention on PPE use. These measures will be obtained at baseline at the individual participant level, after the educational module has been viewed, and at the post-intervention assessment. The mediator analysis will use the measures obtained after the intervention has been delivered. Both measures were validated by expert panel review and discussion with two focus groups of at-risk workers. In prior work, both measures achieved a content validity index of 1 from 3 experts [10].

Knowledge of PPE will be measured using a 10-item chemotherapy exposure questionnaire that assesses knowledge of the 2004 NIOSH alert. The measure was developed by a content expert and study consultant. Each item provides four answer choices with one correct answer for each question. The scale range is 0 to 10, with higher scores reflecting increased knowledge. Perceived risk of drug exposure will be measured using a 3-item subscale from Geer’s Occupational Dermal Survey [21]. A 4-point Likert scale (1 = *strongly disagree*, 4 = *strongly agree*) will be used to assess nurses’ perceptions of the risks of chemotherapy exposure and potential health effects. The score range is 1 to 4. The Cronbach alpha in a similar study population was 0.70 [10].

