#### Sample size considerations and statistical power

The design and sample size for this study were determined in part by power analysis conducted by Optimal Design software [39] that is designed specifically for mixed models such as ours in which nurses are nested within sites that are treated as a random factor. We considered power for detecting a medium sized effect of the intervention and a medium sized multiple correlation (both as defined by Cohen) [40]. We considered scenarios with different numbers of clusters/sites, with different average numbers of nurses per site, and with different levels of the intraclass correlation coefficient (ICC) ranging from 0.01 to 0.03. The ICC will be a measure of the extent that PPE use differs across sites. The higher the ICC, the greater the sample size needed. ICCs of up to 0.03 are common; therefore, we aimed to obtain 80% power for tests with a 2-tailed alpha of 0.05 to detect medium sized effects with this ICC. Analysis revealed that we will obtain this power if our sample includes 11 sites with a mean of 26 participating nurses. In reality, our sites have a mean of 35 nurses (range of 20 to 90), suggesting that we will achieve 80% power even if we have a 25% decrease in the expected sample size (n = 287).

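### Aim 2 tests one summed indirect effect, so it cannot say whether knowledge or perceived risk carries the mediation

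*Protocol article*

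**What the plan says.** The Statistical analysis section of the protocol article sets out two linear mixed models for Aim 2. The first is the Aim 1 model. For the other, "The second model adds the two potential mediators in the first model". The mediation estimate is then defined: "The mediator effect is measured as the difference in the coefficients of the intervention variable between the two models". It receives one 95% confidence interval and one decision rule: "If the confidence interval does not cross zero, it shows that mediation effect is statistically significant".

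The hypothesis attached to Aim 2 is: "The hypothesis is that the effect of the treatment on PPE use will be at least partially mediated by knowledge and perceived risk".

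Elsewhere the two mediators are named separately. The Potential mediators section says: "Both knowledge of PPE and perceived risk of hazardous drug exposure are hypothesized to mediate the potential effects of the intervention on PPE use". The Conceptual framework section lists a rise in knowledge and a rise in perceived risk as items (a) and (b), and adds: "We hypothesize the treatment intervention will result in higher knowledge and perceived risk than the control intervention". No model described under Statistical analysis has knowledge or perceived risk as its outcome.

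**The concern.** The framework names two distinct mechanisms, and the analysis returns one number for both. A significant result could come from knowledge alone, perceived risk alone, or both, and the planned analysis has no means of telling these apart. That matters because the Background says the results are meant to inform nurses, administrators and policymakers on how best to protect workers, and teaching facts and changing risk perception are different programmes.

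The second model does give each mediator's slope on PPE use. Without a model for the effect of treatment on each mediator, those slopes cannot be turned into mediator-specific indirect effects, and the framework's hypothesis that treatment raises each mediator has no stated test.

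**Working it through.** **The plan's own power figure.** The article states: "80% power for tests with a 2-tailed alpha of 0.05 to detect medium sized effects with this ICC". It gives this for 11 sites averaging 26 nurses, and justifies the ICC with "ICCs of up to 0.03 are common". It gives no number for a medium effect; d = 0.5 is assumed here.

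- Variance of the arm contrast: (0.03 + 0.97/26) × (1/5.5 + 1/5.5) = 0.0673 × 0.3636 = 0.0245.
- Noncentrality: 0.5/√0.0245 = 3.20, on 11 − 2 = 9 df.
- Power: 81.1% (80.8% with a 6 v 5 split).

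The stated 80% is reproduced. It concerns Aim 1. No power is stated for Aim 2.

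**What the single difference estimates.** Let a1 and a2 be the arm effects on knowledge and perceived risk, b1 and b2 the mediator slopes in the second model, and c and c′ the arm coefficients without and with the mediators. In linear models with the same covariates and weights,

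c − c′ = a1·b1 + a2·b2.

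With estimated variance components this is approximate, but the estimand is the same sum. With assumed arm effects of 0.5 SD and slopes of 0.3:

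- Knowledge only: 0.5 × 0.3 + 0 = 0.15.
- Perceived risk only: 0 + 0.5 × 0.3 = 0.15.
- Both positive: 0.15 + 0.15 = 0.30.
- Equal and opposite: 0.15 − 0.15 = 0.

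The first two cases are opposite answers to the question of which mediator works, yet they have the same expected value. In simulation (2,000 trials per case, ordinary 95% normal-based intervals) the total was significant in 53.8% and 56.6% of trials respectively, so the planned test does not separate them.

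**Illustrative detection rates.** Set-up: 11 sites of 26 nurses; outcome ICC 0.03; standardised mediators, independent given arm; slopes 0.3; Monte Carlo intervals with 9 df for the arm effects; 95% interval for the total and 97.5% for each specific effect (Bonferroni for two). The document gives none of the path sizes or the mediator ICCs, so all of these are assumptions.

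| Arm effects (knowledge, risk), SD | Mediator ICC | Total | Specific |
|---|---|---|---|
| +0.5, +0.5 | 0.03 | 98% | 69% and 68% |
| +0.3, +0.3 | 0.03 | 67% | 22% and 24% |
| +0.5, 0 | 0.03 | about 45% | 70% (knowledge) |
| +0.5, 0 | 0.10 | about 22% | 32% (knowledge) |
| +0.5, −0.3 | 0.03 | 7 to 9% | 69% (knowledge) |
| +0.5, −0.5 | 0.03 | 2 to 3% | about 70% each |

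The total does better when both paths work in the same direction. The specific test does better when one path is inactive, because the total then carries the noise of the inactive path. The size of either advantage depends on the mediator ICC.

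**The case against.** The Aim 2 hypothesis can be read jointly, and a non-zero total indirect effect answers that reading. Nothing in the article promises to rank or separate the mediators. In the case the protocol expects, with both mediators rising, the planned test is the stronger one. All of this stands, and it is why the total should be kept.

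It can also be said that the article is condensed and that mediator models may sit in an unseen analysis plan. That is fair for models that are merely unmentioned. The article does, however, fix the Aim 2 estimand and its decision rule, and the estimand it fixes is the sum.

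Three stronger readings are tempting, and the document does not support them.

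- *That entering both mediators together is an error.* It is not. Specific indirect effects need the same joint outcome model. The weakness lies in reducing it to one number.
- *That the plan would declare no mediation when the interval crosses zero.* The article defines only the positive conclusion.
- *That cancellation is the likely outcome.* It needs indirect effects of opposite sign and is complete only if they are equal in size. The Conceptual framework expects treatment to raise both mediators. One could imagine feedback of few spills or low drug levels lowering perceived risk, but that is conjecture.

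**Conclusion.** The point holds in limited form. The planned difference in coefficients is a valid estimate of the total indirect effect, under the usual no-confounding assumptions for mediation. It cannot say which mediator carries the effect, whatever the data show; that conclusion rests on algebra and not on the simulation. Nor does any stated model test whether treatment raises each mediator.

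The effect on power runs both ways: a gain for the total if both mediators rise (about 98% against 68%), and a loss if only one is active (about 45% against 70%, or 22% against 32% at a mediator ICC of 0.10). These percentages rest on assumed path sizes and ICCs. Cancellation is a secondary risk. This is a worthwhile, inexpensive improvement to a secondary aim and has no bearing on the Aim 1 result.

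**What to change.** Keep the planned difference as the total indirect effect, and keep both mediators in the outcome model. Then add:

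1. A linear mixed model for each mediator with a random intercept for site, and with arm and that mediator's baseline value as predictors. Report the two arm effects, which test the framework's hypothesis directly.
2. Two specific indirect effects, each the arm effect on the mediator times that mediator's slope in the outcome model.
3. A Monte Carlo or site-level interval for each, suited to 11 clusters, with multiplicity over the two mediators controlled.
4. A statement that the total addresses joint mediation and the specific effects address attribution. If covariates differ between the mediator and outcome models, the two specific effects will not add exactly to the planned difference; say so.

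The cost is two extra models and a few lines of text. Baseline and post-intervention measures of both mediators are already scheduled. The downside is that each specific test has less power than the total when both mediators work in the same direction.

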**Methods/Design:**

The DEFENS Study is a cluster randomized controlled trial. We are enrolling cancer centers and will recruit nurse participants in April 2015. Eligible cancer centers employ at least 20 eligible registered nurses in the chemotherapy infusion setting and have on-site phlebotomy resources. Eligible participants are nurses who work at least 0.40 full-time equivalent hours in the chemotherapy infusion setting and have not received an antineoplastic drug for a health problem in the past year. An encrypted, user-authenticated website will administer surveys and deliver control and treatment interventions. The primary endpoint is the change in score on nurses’ reports of the Revised Hazardous Drug Handling Questionnaire between baseline and approximately 18 months later. A baseline survey is completed after informed consent and is repeated 18 months later. Nurses in all sites who experience a drug spill will also report incidents as they occur; these reports inform the treatment intervention. Plasma will be obtained at baseline, approximately 18 months later (the primary endpoint), and with drug spill occurrences to measure hazardous drugs levels and to inform the treatment intervention. Potential mediators include knowledge of hazardous drug handling and perceived risk of drug exposure. We will examine whether personal factors and organizational factors moderate the intervention effects.

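### The Aim 3 moderation model is listed without the baseline PPE score and without a tie to the Aim 1 model; fitted as listed, its product-term tests forgo precision, by an amount set by a correlation that the article does not give

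*Protocol article*

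**What the plan says.** All of the modelling text stands under Statistical analysis in the protocol article.

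- **Aim 1.** PPE questionnaire data and demographic variables are "included in the fixed-effect structure to increase the precision of estimates". The word baseline is not used. It is the sensible reading, since the follow-up questionnaire is the outcome.
- **Aim 2.** The link is explicit: "The first model is the same model we use in Aim 1". The mediators are then added.
- **Aim 3.** The mixed models "include receipt of the treatment intervention, the moderator variables, and the products of treatment intervention receipt with the moderator variables as predictors of PPE use". No baseline score is named and there is no link to Aim 1.

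The abstract defines the outcome as a change: "The primary endpoint is the change in score on nurses’ reports of the Revised Hazardous Drug Handling Questionnaire between baseline and approximately 18 months later". The Aim 1 and Aim 3 text speaks only of PPE use scores or PPE use. According to Randomization, sites are allocated after participants have enrolled and completed the baseline survey, so the baseline score exists before allocation. Potential moderators makes workload, practice environment and safety organizing site means, while experience, education and certification are collected from each nurse.

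**The concern.** The article states a precision covariate set for one aim, carries it over for the second and writes a separate predictor list for the third. An analyst who fits Aim 3 as listed would test the product terms without the baseline PPE score. If the outcome is then the 18-month score, baseline PPE use is nowhere in the analysis, although the endpoint is described as a change from baseline.

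Moderation is one of the three specific aims. The sample size section states power for a medium intervention effect and a medium multiple correlation, but for no interaction. Interaction tests usually have less power than the main comparison, so precision given up there matters. The covariate set is also best settled before results are known.

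**Working it through.** **Inputs from the article.** Two-sided alpha 0.05 and 80% power ("we aimed to obtain 80% power for tests with a 2-tailed alpha of 0.05 to detect medium sized effects with this ICC"); 11 sites with a mean of 26 nurses ("Analysis revealed that we will obtain this power if our sample includes 11 sites with a mean of 26 participating nurses"); ICC 0.03, the top of the range considered; 382 nurses expected, or 287 after a 25% loss.

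**Assumptions, not in the article.** A medium effect is taken as 0.5 SD. The correlation r between baseline and 18-month score is varied over 0.3, 0.5 and 0.7. The nearest stated figure, a test-retest kappa of 0.80 for the original scale, is not an 18-month correlation. Interaction sizes are illustrative.

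**1. The plan's own figure.** Variance of the arm difference = 4 × (0.03 + 0.97/26)/11 = 0.0245, so SE = 0.156. With d = 0.5 and a noncentral t on 11 − 2 = 9 df, power is 81.1% (80.8% with a 5:6 split). The stated 80% reproduces.

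**2. Effect of adding baseline on the SE.** For a follow-up-score outcome, adjusted SE / unadjusted SE = √(1 − r²). For a change-score outcome the unadjusted variance is proportional to 2(1 − r), so the ratio is √((1 + r)/2).

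| r | SE cut, follow-up score | SE cut, change score |
|---|---|---|
| 0.3 | 4.6% | 1 − √0.65 = 19.4% |
| 0.5 | 13.4% | 13.4% |
| 0.7 | 28.6% | 7.8% |

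For the follow-up score, seen from the other side, omitting baseline makes the SE about 5%, 15% or 40% larger than the adjusted one.

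**3. A nurse-level example, follow-up score.** Take a 50/50 nurse factor and a difference in intervention effect of 0.4 SD. SE of the product = √(16 × 0.97 × (1 − r²)/N), and power = Φ(0.4/SE − 1.96). With N = 382 and no baseline, SE = √(15.52/382) = 0.202.

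| N | No baseline | r = 0.3 | r = 0.5 | r = 0.7 |
|---|---|---|---|---|
| 382 | 51% | 55% | 63% | 79% |
| 287 | 41% | 44% | 51% | 67% |

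**4. How general that gain is.** If unadjusted power is p, adjusted power is Φ((z_p + 1.96)/√(1 − r²) − 1.96), where z_p is the standard normal quantile of p. The gain in percentage points is:

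| Unadjusted power | r = 0.3 | r = 0.5 | r = 0.7 |
|---|---|---|---|
| 10% | 0.6 | 2.0 | 5.6 |
| 20% | 1.5 | 5.2 | 14.7 |
| 50% | 3.8 | 11.9 | 28.4 |
| 60% | 4.1 | 12.4 | 27.3 |
| 90% | 2.5 | 6.3 | 9.5 |

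The example in step 3 therefore sits close to the most favourable point. With a change-score outcome the largest gain is about 12 points at r = 0.5 and 7 at r = 0.7.

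**5. Site-level moderators.** Variance of the product = (4/11) × (0.03(1 − r_B²) + 0.97(1 − r_W²)/26), where r_B and r_W are the between-site and within-site correlations. Take an interaction of 0.3 SD per SD of the moderator. One moderator leaves 7 df; all three with their products leave 3 df.

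| Model | No baseline | Baseline explains within-site variance only (r_W = 0.5 to 0.7) | Explains both levels equally (0.5 to 0.7) |
|---|---|---|---|
| One moderator, 7 df | 38% | 43-49% | 48-64% |
| Three moderators, 3 df | 27% | 30-35% | 34-45% |

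In this example, even the best case stays below 80%.

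**The case against.** The strongest reply is that nothing was dropped. The Aim 3 sentence says what the models include, not that these are the only terms. It does not repeat the random site intercept either, which is set out once for all models. A journal article may also leave the covariate list of a secondary model to the full plan. This stands to the extent that a reader who infers a deliberate exclusion of the Aim 1 covariates goes further than the text. What remains is that the article does specify the Aim 1 covariates and does carry them into Aim 2, but gives Aim 3 a separate list with no such link. That is wording to correct, and more than a detail left unsaid.

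A reader might also infer that Aim 3 lacks demographic adjustment altogether. The article does not support that: experience, education and certification enter as moderator main effects. Table 1 lists demographics separately from moderators, but Table 3 names no further personal variables, so which demographics would be lost cannot be shown.

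Finally, a chance difference between arms in how a moderator relates to baseline PPE use is sampling error and is reflected in the SE. It does not bias the product term or invalidate its test. This objection stands in full; the point concerns precision only.

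**Conclusion.** The point holds as a precision and consistency issue in Aim 3. It does not touch the Aim 1 analysis or the sample size. Fitted as listed, the product-term tests forgo precision under either reading of the outcome, except that the loss on a follow-up score becomes negligible as r approaches zero and the loss on a change score as r approaches one.

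It would be tempting to say that every interaction test loses 10 to 30 points of power. The article does not support that. Such figures need r of about 0.5 to 0.7, a follow-up-score outcome, a nurse-level moderator and unadjusted power in the middle of the range. At r = 0.3 the follow-up-score gain never exceeds about 4 points. Three of the six moderators are site means, for which the benefit turns on an unknown between-site correlation and the number of sites is the tighter constraint.

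**What to change.** In the Aim 3 paragraph under Statistical analysis, state: the Aim 3 models are the Aim 1 model (baseline PPE score, demographic fixed effects not already entered as moderators, random site intercept) plus the moderator main effects and their products with allocated arm. In the Aim 1 sentence, say that the PPE questionnaire covariate is the baseline score.

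With baseline in the model, the arm and product coefficients are the same whether the outcome is written as the 18-month score or as the change, so the same sentence removes that ambiguity from Aim 3. The cost is a line or two of analysis text, with no new data and one further fixed-effect coefficient for the baseline score. Any precision gain quoted alongside it should be shown as a range over assumed r.
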